## Methods/design

The current study is a non-inferiority, multicenter, randomized, controlled clinical trial with two treatment groups: UP in group format and traditional CBT in individual format (treatment as usual, TAU). A conservative, non-inferiority design was selected because, to the best of our knowledge, this is the first randomized controlled trial to compare the UP in a group format against individual CBT in public mental health settings.

In the present investigation, all consecutive patients with EDs attending any of the collaborating centers (see “Sample and recruitment” section) are asked to participate. Once inclusion criteria are met (see “Inclusion and exclusion criteria” section), each patient is randomly assigned to one of the two experimental groups: TAU or UP (see “Procedure” section). The study includes 5 assessment points (baseline, post-treatment, and three follow-ups at 3, 6, and 12 months after treatment completion). The flow chart of study design is shown in Fig. 1. Also, a schedule of enrolment, interventions, and assessments is reported following the Standard Protocol Items: Recommendations for Interventional Trials (SPIRIT) guidelines (Fig. 2). Note that, despite treatment occurs at different frequencies between conditions (approximately once a month in the TAU condition and weekly in the UP group), assessment points are the same for both groups.

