Enrollment period and waiting time are comparable across participants (2–3 weeks). When the time from assessment, diagnosis, and randomization to the onset of the intervention takes more than 2 weeks we establish a new period of assessment. For ethical reasons, if a patient feels uncomfortable with the group format at any time during the study, he/she is allowed to join the TAU condition. This information is collected and considered in the analyses.

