### Sample size

To calculate the sample size required, the non-inferiority margin (i.e., tolerable amount of effect difference between TAU and the UP) has to be set. This was done according to the US Food and Drug Administration (FAD) [16] guidelines. First, the effect of the active control (i.e., CBT) compared with placebo needs to be established, based on previous research. Meta-analyses indicate medium-to-large effect sizes (between .4 and .8) of individual CBT on EDs [17–19]. Then, an amount of minimum preserved effect needs to be set. According to FDA guidelines, a preserved effect of a 50% of the effect of the active control (individual CBT) is recommended, so this was set to .3 in the present study. Because, to the best of our knowledge, no meta-analysis has reported effect sizes for each outcome included in the study, the margin has been defined according to the pooled estimate of overall effectiveness of CBT.

With regards to treatment satisfaction, a 35% non-inferiority margin was established. This is based on a meta-analysis of computer CBT, in which between 70% and 100% of depressed patients were satisfied with treatment [20]. To the best of our knowledge, there is no meta-analysis of treatment satisfaction with individual, face-to-face CBT and its study is rare. However, similar to group UP, computer CBT has been argued to be an alternative to traditional CBT [20], especially when resources are limited, so the aforementioned satisfaction rates of computer CBT might be relevant in the present study.

We obtained a sample size of 95 participants for each group with 80% power, an alpha level of .05 (one-sided), a standard deviation of .83 in the CBT group compared with placebo, and a non-inferiority limit of .30 [21, 22]. Considering a drop-out of 15%, we decided to recruit 110 subjects in each group. When registering the study, a sample size of 200 individuals was calculated. However, this was increased by 20 patients after considering non-inferiority sample size calculations.

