### Eligibility criteria

Inclusion and exclusion criteria were set following the recommendations made by the authors of the UP [27] (Table 1).

**Table 1 Tab1:** Eligibility criteria

Inclusion criteria	
1	Anxiety disorder, mood disorder, or adjustment disorder is the main diagnosis (most interfering and severe)^a^
2	The patient is over 18 years of age
3	The patient is fluent in the language in which therapy is performed (Spanish in the present study)
4	The patient is able to attend to the evaluation and treatment sessions and signs the informed consent form
5	Patients taking pharmacological treatment for their emotional disorder are asked to maintain the same dosages and medications for at least 3 months prior to enrolling in the study and during the whole treatment^b^
Exclusion criteria	
1	The patient presents a severe condition that would require to be prioritized for treatment, so that an interaction between both interventions cannot be ruled out. These include a severe mental disorder (bipolar disorder, schizophrenia, or an organic mental disorder),suicide risk at the time of assessment, or substance use in the last three months (excluding cannabis, coffee, and / or nicotine)
2	The patient has previously received 8 or more sessions of psychological treatment with clear and identifiable CBT principles within the past 5 years.

^a^The following disorders will be included based on DSM-IV-TR diagnostic criteria [21]: major depression disorder, dysthymic disorder, panic disorder, agoraphobia, obsessive-compulsive disorder, generalized anxiety disorder, posttraumatic stress disorder, social anxiety disorder, hypochondria, and adjustment disorders. Patients with unspecified anxiety disorders and unspecified depressive disorders will also be included as they are frequent in public settings

^b^If medication stability is not possible, the participant’s data will be treated separately in the analyses

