### Treatment as usual (TAU)

Individual CBT is the treatment of choice by psychologists and psychiatrists at the collaborating Public Mental Health Centers and Primary Care Centers, together with pharmacological treatment (i.e., antidepressants and / or anxiolytics). Clinicians in this condition complete a self-report sheet describing the characteristics of their interventions with treatment modules as cues (psychoeducation module, identification of negative thoughts, breathing training, etc.), the average duration of sessions, number of sessions delivered, and end-of-treatment date, as well as information on the number of appointments with the psychiatrist and pharmacological treatment prescribed during the study. Information on the number of appointments with the psychiatrist and pharmacological treatment prescribed during the study is also collected for patients in the UP group following the same procedure described for the CBT condition.

As opposed to the UP condition, in which the duration of treatment is fixed (12 sessions), the usual practice in Spanish public settings is that treatment ends when both the clinician and the patient agree that the intervention has been effective. This is not necessarily guided by questionnaires or a diagnostic interview, but on clinical judgment. Because the study goal is to compare a new treatment (UP in a group format) with the usual practice in Spanish public settings, the same procedure described above will be used to determine the end of treatment in the TAU condition and no specific end points (i.e., a decrease in questionnaire scores) or number of sessions will be imposed. Because this is likely to yield different treatment durations between study conditions, the treatment duration (number of sessions) will be used as a covariate in the analyses.

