### Analyses

First, we will calculate between-group differences in baseline measures, to ensure that randomization resulted in comparable groups. When normally distributed, continuous data will be analyzed via *t* test. If the Kolmogorov-Smirnov test indicates a non-normal distribution, a Mann-Whitney *U* test will be preferred. A chi-square test will be performed for categorical data. Then, to compare the efficacy of treatments, we will use a mixed-effects regression modeling with full information maximum likely hood estimation. This method is recommended over repeated-measures ANOVAs due to its flexibility in handling missing data [39]. Group (TAU or UP) will be used as the between-subject factor and time (baseline, post-treatment, and follow-ups) as the within-subject factor. Standardized effect sizes (Cohen’s *d*) will be calculated both for within and between-group analyses. Covariates will be demographic and clinical variables that are not comparable between groups, as exposed in the beginning of this section. Effect estimators in the UP group will be adjusted to control for the impact of group dependencies (i.e., homogenization of response to treatment due to shared environment), following the recommendations of Baldwin et al. [40].

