To address problems of missing data or premature dropouts, an intention-to-treat analysis will be used and the most recent data will be imputed (last observation carried forward approach). This analytic strategy will only be performed with patients attending at least 50% of sessions, as recommended in past research [41], and with those responding to at least one of the post-treatment assessments (i.e., end of treatment or follow-ups) so that treatment effect may be captured by the last observation. In addition to the last observation forward, missing data in the UP group will also be replaced with the CBT mean +/− the non-inferiority margin and missing data in the CBT group will be replaced with the UP mean (i.e., bias toward inferiority) [42]. Results using a last observation carried forward approach and a bias toward inferiority imputation will be compared against a completers-only strategy and all of them will be reported. To ensure non-inferiority, a per-protocol analysis will also be conducted. Following FDA guidelines [16], non-inferiority will be concluded if the upper bound of the 95% CI for the effect estimate in the UP condition is smaller than the non-inferiority margin (50% of the effect estimate of individual CBT when compared to placebo). Due to the non-inferiority design (i.e., the Unified Protocol in a group format is not worse than individual CBT), a one-sided confidence interval will be used in the analyses. A post-hoc power analysis with the primary outcomes will be conducted at post-treatment and follow-ups using the sample size and obtained effect size.

The researcher analyzing data, [name], will be blind to arm allocation. To ensure that, arms will be given arbitrary letters (A and B) in the database and only the lead researcher, [name], will know the correspondence between study allocation arms and assigned arbitrary letters.

Reporting of results will follow the Consolidated Standards of Reporting Trials (CONSORT) recommendations [43].

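### The analysis called intention-to-treat is filtered on attendance and response after randomisation, its 50% rule has a planned denominator only in the UP arm, and no set is named to decide non-inferiority

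*Protocol article*

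**What the plan says.** All references are to the Protocol article.

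- **Analyses, model.** Treatments are compared by "mixed-effects regression modeling with full information maximum likely hood estimation", chosen for its handling of missing data. No attendance condition is attached to this model.
- **Analyses, missing data.** For an analysis called intention-to-treat, "the most recent data will be imputed (last observation carried forward approach"). The next sentence limits it: "This analytic strategy will only be performed with patients attending at least 50% of sessions", and also to patients with at least one end-of-treatment or follow-up assessment. The reason given is that the last observation should be able to capture a treatment effect.
- **Analyses, other sets.** A second imputation, biased toward inferiority, fills missing values. LOCF, this imputation and a completers-only analysis are to be compared and all reported. A per-protocol analysis is added. Non-inferiority is concluded from a confidence bound against the margin, but the text does not say in which set.
- **Unified protocol in group format.** There are 12 sessions.
- **Treatment as usual (TAU).** In this arm "no specific end points (i.e., a decrease in questionnaire scores) or number of sessions will be imposed".
- **Sample and recruitment.** A patient uncomfortable with the group may leave it: "he/she is allowed to join the TAU condition". The switch is recorded and considered in the analyses; how is not stated.
- **Eligibility criteria, Table 1 footnote b.** Where medication cannot be kept stable, the participant's "data will be treated separately in the analyses".
- **Discussion, limitations.** A preference for individual treatment is expected to be a possible cause of dropout or poorer results in UP.

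**The concern.** Attendance and returning an assessment both happen after randomisation, and treatment can affect both. A set defined by them loses the protection that an intention-to-treat analysis is meant to give.

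The attendance rule is also not the same rule in the two arms. In UP, 50% of 12 is 6 sessions. In TAU the number of sessions is whatever clinician and patient settle on, so there is no planned total to take half of. Suppose the rule is counted against sessions actually delivered. A patient who stops after 4 sessions then fails in UP (4/12 = 33%) but passes in TAU (4/4 = 100%). The plan does not say whether it is counted that way.

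The Analyses section does not say how LOCF fits with the full-information mixed model, which was chosen because it deals with missing data. LOCF holds an early score constant to 12 months, so later relapse cannot appear, and it treats filled values as if they were observed.

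A non-inferiority conclusion is usually checked in an intention-to-treat and a per-protocol set. If both are filtered on adherence, the second gives little independent check on the first.

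**Working it through.** **1. The plan's own figure.** The Sample size section states: "We obtained a sample size of 95 participants for each group with 80% power, an alpha level of .05 (one-sided"), with SD 0.83 and a limit of 0.30.

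n per arm = 2 × (1.645 + 0.842)² × 0.83² / 0.30² = 94.7, so 95. This reproduces. For 15% drop-out, 95 × 1.15 = 109.3, which gives the stated 110; 95 / 0.85 = 111.8 would give 112. The sample size is not in dispute here.

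**2. Set-up for the filter.**

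- From the plan: 110 per arm, SD 0.83, margin 0.30, one-sided alpha 0.05.
- Assumed, because the plan gives no values: exclusion rates dUP and dTAU, and g, the amount by which excluded patients do worse than retained ones, in the units of the margin.
- The true difference among all randomised patients is set at the margin (UP worse by 0.30), so a valid test concludes non-inferiority 5% of the time.

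In each arm, overall mean = retained mean + d × g (higher is worse). Hence:

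- Retained difference = 0.30 − g × (dUP − dTAU)
- SE = 0.83 × √(1/[110(1 − dUP)] + 1/[110(1 − dTAU)])
- P(conclude non-inferiority) = Φ((0.30 − retained difference)/SE − 1.645)

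**3. One case in full.** Take dUP = 15%, dTAU = 0, g = 0.50.

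- Retained difference = 0.30 − 0.075 = 0.225
- SE = 0.83 × √(1/93.5 + 1/110) = 0.117
- P = Φ(0.075/0.117 − 1.645) = Φ(−1.00) = 15.8%

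**4. Range.** Probability of false non-inferiority:

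| Excluded, UP / TAU | g = 0.30 | g = 0.50 | g = 0.83 |
|---|---|---|---|
| 20% / 10% | 8.1% | 10.9% | 16.8% |
| 15% / 0% | 10.4% | 15.8% | 28.1% |
| 30% / 15% | 9.8% | 14.5% | 25.1% |
| 25% / 5% | 12.4% | 20.4% | 38.7% |
| 15% / 15% | 5.0% | 5.0% | 5.0% |
| 10% / 20% | 2.9% | 2.0% | 1.0% |

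A further case: 15% leave each arm and the leavers have the same mean outcome in both arms. The retained difference is then 0.30/0.85 = 0.353 and the probability is 1.9%.

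**5. What the other planned analyses cover.**

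- The imputation biased toward inferiority replaces missing values. A low attender with observed scores has nothing missing. The text does not say that the imputation reaches patients removed by the attendance rule.
- Completers-only and per-protocol sets leave out non-adherers by design.
- The mixed model carries no stated filter, but neither is it stated to include every randomised patient or to be the deciding analysis.

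The calculation is a normal approximation. It keeps SD 0.83 in the retained set and ignores clustering within therapy groups.

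**The case against.** The strongest reply is that the filtered LOCF analysis is one of several. Directly after it, the plan adds an imputation designed to count against UP, promises to report all the results side by side, and adds a per-protocol analysis. The stated reason for the filter is specific to LOCF, so it may not touch the mixed model at all. This is a real counterweight and it stands. It does not answer which analysis decides, or whether any of them covers all randomised patients.

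Three stronger readings are tempting, and the documents do not support them.

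- *The filter biases the trial toward non-inferiority.* As worded it applies to patients in both arms. A missing denominator in TAU does not mean that no TAU patient is excluded, and the one-assessment condition applies to both arms. The Sample size section uses a single 15% drop-out for both groups. The option to leave the group and the format preference noted in the Discussion make heavier UP exclusion plausible, but neither is quantified. If medication changes were more frequent in TAU, footnote b would set aside more TAU patients.
- *No analysis contains all randomised patients.* The text shows only that none is stated to.
- *Patients who switch from UP to TAU are removed.* The plan says that switching is considered in the analyses. It gives no rule for counting a switcher's sessions, and treating data separately need not mean exclusion from every main analysis.

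It is also fair to say that the mixed model is no complete cure. It assumes data missing at random, and a patient without any post-treatment assessment contributes only baseline data.

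**Conclusion.** The point holds as a defect of definition. The set is mislabelled as intention-to-treat, its attendance rule has a planned denominator only in UP, and the set that decides non-inferiority is not named. These follow from the text and need no assumption.

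The effect on the conclusion is conditional. Under the assumed UP-heavy exclusions of poor outcomes, false non-inferiority is about 8% to 39% instead of 5%. It stays at 5% with equal exclusion and equal g, and falls to 1% to 3% with TAU-heavy exclusion. The exclusion rates and g are assumptions throughout. The supported statement is that the direction of bias is uncontrolled and can lean toward non-inferiority, not that it does.

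**What to change.** 1. Define the intention-to-treat set as all randomised patients in their allocated arm, whatever their attendance, switching or medication change.
2. Make the mixed model already planned, fitted to all available data in that set, the primary analysis. Keep using post-treatment assessments from low attenders and switchers.
3. Apply the imputation biased toward inferiority to all randomised patients as a sensitivity analysis, because the mixed model assumes data missing at random.
4. Do not let LOCF be primary.
5. Move the attendance rule, with a definition that works in TAU, and the medication-stable subset to the per-protocol or sensitivity analyses.
6. State that the intention-to-treat and per-protocol analyses must both meet the margin.

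**Cost.** Mostly wording, since the model and the imputation are already planned. Expect slightly wider intervals and a little more analysis work. The gain depends on outcomes from low attenders and switchers being collected and kept.

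### The imputation labelled as biased toward inferiority fills missing TAU values with the UP mean, so at the margin it can be easier to pass than completers-only when TAU loses about as many patients as UP, or more

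*Protocol article*

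**What the plan says.** The Analyses section of the protocol article plans three ways of handling missing outcomes: last observation carried forward, a second imputation, and completers-only. All three are to be reported, with a per-protocol analysis in addition. None is named as decisive.

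The second imputation has two halves. The rule for the group-format arm is "missing data in the UP group will also be replaced with the CBT mean +/− the non-inferiority margin". The rule for the comparator arm is "missing data in the CBT group will be replaced with the UP mean (i.e., bias toward inferiority". The label presents the pair as a stress test against UP.

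The decision rule compares an upper confidence bound with the margin, and the same section specifies that "a one-sided confidence interval will be used in the analyses". The Sample size section sets the planning size and error rate: "We obtained a sample size of 95 participants for each group with 80% power, an alpha level of .05 (one-sided". For the spread of the outcome and the margin, the inputs were "a standard deviation of .83 in the CBT group compared with placebo, and a non-inferiority limit of .30". Losses are then allowed for as follows: "Considering a drop-out of 15%, we decided to recruit 110 subjects in each group".

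**The concern.** In a non-inferiority trial the error to guard against is declaring UP non-inferior when it is worse than TAU by the margin or more. A conservative imputation should make that harder. Giving missing TAU patients the UP mean does the opposite when UP is worse, because it moves TAU toward the poorer arm and narrows the gap. Pulling toward no difference is conservative for a superiority claim but not for non-inferiority.

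The UP half does not compensate at the margin. If UP is worse by exactly the margin, the CBT mean plus the margin already is the UP mean, so nothing is added. In both arms a single constant stands in for each missing patient, and if these constants are analysed as observed data the standard error falls below that of completers-only.

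A reader of the trial report would naturally treat a pass under this label as the strongest evidence of robustness. If the check is easier to pass than completers-only, that inference is wrong.

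**Working it through.** **Inputs.** From Sample size: SD s = 0.83, margin M = 0.30, N = 110 per arm, 15% drop-out, one-sided alpha .05. From Analyses: the two fill rules and the one-sided 95% upper bound. Assumptions: higher scores are worse (as on BDI-II and BAI), the sign in the UP rule is plus, data are missing at random, filled values count as observed, and two arms are compared at one time point without clustering. The protocol does not say how drop-out splits between the arms, so a range is shown.

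**The protocol's own figure.** With a true difference of 0 (not stated, but it reproduces the result), n = 2(1.645 + 0.842)² × 0.83² / 0.30² = 94.7, or 95 per group. This matches.

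**Effect on the estimate.** Let D be the UP minus TAU difference among observed patients, and f_U and f_T the missing shares. After filling:

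- UP mean = (1 − f_U)·UP + f_U·(TAU + M)
- TAU mean = (1 − f_T)·TAU + f_T·UP
- difference = (1 − f_U − f_T)·D + f_U·M

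At D = M this is (1 − f_T)·M, so the shift at the margin depends only on TAU losses. With 15% missing per arm it is 0.85 × 0.30 = 0.255.

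**Effect on the standard error, 15% per arm.** Completers-only: 0.83 × √(2/93.5) = 0.121. Filled data at D = M: the UP variance is 0.85 × 0.6889 = 0.5856, the TAU variance is 0.5856 + 0.15 × 0.85 × 0.09 = 0.5970, and the model SE is √(1.1826/110) = 0.104. The filled estimate itself varies with SD (1 − 0.30) × 0.121 = 0.085.

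**False non-inferiority rate, 15% per arm.** Φ[(0.30 − 0.255 − 1.645 × 0.1037)/0.0850] = Φ(−1.48) = 7.0%. Simulation gives 6.9% with fixed missing counts and 7.3% with random counts. Completers-only gives 5.0%.

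**Range at the margin** (one-sided 5%):

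| Missing UP / TAU | SD | Expected estimate | Formula | Simulation, random counts |
|---|---|---|---|---|
| 5% / 5% | .83 | 0.285 | 5.6% | 5.8% |
| 15% / 15% | .83 | 0.255 | 7.0% | 7.3% |
| 30% / 30% | .83 | 0.210 | 11.0% | 12.4% |
| 10% / 30% | .83 | 0.210 | 15.7% | 16.6% |
| 20% / 10% | .83 | 0.270 | 5.0% | 5.1% |
| 30% / 10% | .83 | 0.270 | 3.7% | 3.8% |
| 15% / 15% | 1 | 0.255 | 5.9% | 6.2% |
| 30% / 30% | 1 | 0.210 | 6.7% | 7.4% |

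**Away from the margin, 15% per arm, SD .83.** The chance of declaring non-inferiority is 84% against 80% for completers-only at a true difference of 0, and 41% against 34% at 0.15.

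**Which parts matter.** At 15% per arm, the same pull with the completers' SE of 0.121 would give 3.4%. The smaller SE with missing TAU values filled by the CBT mean instead would give 5.0%. The inflation needs both the pull and the smaller SE.

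**The case against.** Several objections have force.

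**Direction of drop-out.** The Discussion names dropout as a possible result of assigning people who prefer individual treatment to the group format. That points to heavier losses in UP, where the inflation disappears (5% at UP 20%/TAU 10%) or reverses (4% at UP 30%/TAU 10%). A reader might infer that the rule always inflates false non-inferiority; the figures do not support that. But the protocol fixes no split, and a safeguard should not depend on one.

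**Standard error.** The article does not say how it is computed and cites a source for the method. With a suitable variance the rule could be conservative. Replacing values with a mean is most naturally read as a constant fill, so the concern stands as conditional on that reading. Nor is the interval too narrow for the filled estimate: the model SE (0.104) exceeds the estimate's own SD (0.085). It is narrow relative to completers-only and is centred on a value pulled below the margin.

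**The plus-or-minus sign.** A reader might take the minus sign to apply to BDI-II and BAI, which would give an error of about 31% at 15% missing per arm. The rule's own label rules that out. The secondary outcomes run in both directions, so the sign most plausibly follows each scale. It should be stated, but the 31% is not evidence against the plan.

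**Weight and scale.** This is one of several reported analyses, beside a likelihood-based mixed model and a per-protocol analysis. If the restriction to patients with at least 50% attendance and one post-treatment assessment also covers this imputation, the missing share would be smaller; at 5% per arm the error is under 6%. The UP half does penalise UP below the margin, and the point estimate moves in UP's favour only when the difference exceeds half the margin. All of this limits the harm without removing the mismatch between label and behaviour.

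**Conclusion.** The point holds in a limited form. The UP-mean fill for missing TAU values does not do what its label says. At planned drop-out split equally, the false non-inferiority rate at the margin is about 7% instead of 5% (about 6% at SD 1). It grows when TAU loses more patients than UP, and it vanishes or reverses when UP loses about two to three times as many as TAU.

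This rests on data missing at random, constants analysed as observed, and a single-time-point comparison; the planned repeated-measures model and the clustering within therapy groups were not modelled. It would be wrong to infer that the trial's non-inferiority conclusion as a whole is invalid, because the protocol does not make this analysis decisive. The harm is that a pass could be cited as confirming robustness when the check may be easier to pass than completers-only. It should be fixed before analysis; it is not a must-fix.

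**What to change.** Delete the rule that fills missing TAU values with the UP mean. Impute missing TAU values from the TAU distribution, and missing UP values from the TAU distribution shifted by the margin in the worse direction. Use multiple imputation pooled by Rubin's rules. State the sign of the shift for each outcome: plus on BDI-II and BAI, and the opposite on scales where higher is better.

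Under missing at random this is unbiased at the margin and conservative for true differences below it. It is not conservative above the margin, where the shifted values would flatter UP. As an indication, a single-value version of the fix (missing TAU = CBT mean, missing UP = CBT mean plus margin) with 15% missing per arm gives a 5.0% error at the margin and 79% power at true equality, in line with completers-only.

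The cost is a reworded sentence, a routine multiple-imputation run and slightly wider intervals. Recruitment, treatment and data collection are unaffected. If the present rule is kept, its label should be dropped.

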**Methods:**

The study is a multicenter, randomized, non-inferiority controlled clinical trial. Participants will be 220 individuals with emotional disorders, who are randomized to either a treatment as usual (individual cognitive behavioral therapy) or to a Unified Protocol condition in group format. Depression, anxiety, and diagnostic criteria are the primary outcome measures. Secondary measures include the assessment of positive and negative affect, anxiety control, personality traits, overall adjustment, and quality of life. An analysis of treatment satisfaction is also conducted. Assessment points include baseline, post-treatment, and three follow-ups at 3, 6, and 12 months. To control for missing data and possible biases, intention-to-treat and per-protocol analyses will be performed.

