### Primary outcomes

Severity of depression and anxiety symptoms are assessed with the Beck Depression Inventory (BDI-II) [23, 24] and the Beck Anxiety Inventory (BAI) [25, 26], respectively.

In addition to symptoms, a current diagnosis of anxiety and/or mood disorder is made with the lifetime version of the Anxiety Disorders Interview Schedule for DSM-IV (ADIS-IV-L) [4, 29]. The ADIS-IV-L is a semi-structured interview based on the diagnostic criteria of the Diagnostic and Statistical Manual of Mental Disorders -4th ed. (DSM-IV-TR) [4]. We have not used the ADIS-5 because it is not available in Spanish yet.

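### The non-inferiority rule is worded on an effect within the UP arm instead of the UP-TAU difference, names no deciding outcome or visit, and has no margin for the binary primary outcome

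*Protocol article*

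**What the plan says.** The decision rule is in the Analyses section of the protocol article: "non-inferiority will be concluded if the upper bound of the 95% CI for the effect estimate in the UP condition is smaller than". The limit it then names is the margin, described there as half of the effect of individual CBT over placebo. The same paragraph adds that "a one-sided confidence interval will be used in the analyses".

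The Sample size section defines the quantity being bounded: "non-inferiority margin (i.e., tolerable amount of effect difference between TAU and the UP". It uses one margin for all efficacy outcomes, since "the margin has been defined according to the pooled estimate of overall effectiveness of CBT". It then reports the calculation: "We obtained a sample size of 95 participants for each group with 80% power, an alpha level of .05 (one-sided"; the other inputs are "a standard deviation of .83 in the CBT group compared with placebo, and a non-inferiority limit of .30". The only other margin is 35%, and it is for treatment satisfaction.

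The Abstract lists three primary outcomes: "Depression, anxiety, and diagnostic criteria are the primary outcome measures". Under Primary outcomes, the first two are the BDI-II and BAI scores. The third is categorical: "a current diagnosis of anxiety and/or mood disorder is made with the lifetime version" of the ADIS-IV. The Methods/design section sets five assessments, four of them after baseline. None is called primary.

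**The concern.** The rule decides the headline claim of the trial, and three things in it do not fit the rest of the document.

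- **Quantity.** A margin that limits the loss against TAU has to be compared with the UP-TAU difference. An effect in the UP condition is, on its face, a change within one arm. The Analyses section plans both within-group and between-group effect sizes, so both numbers will exist.
- **Deciding test.** The rule names neither an outcome nor a visit, and does not say whether one success is enough or all are required. The sample size covers one continuous comparison. Depending on the reading, either the type I error or the power differs from what is stated.
- **Diagnosis.** A margin of .30 paired with an SD of .83 belongs to a continuous measure and cannot be applied directly to a proportion who still meet diagnostic criteria. Satisfaction was given a percentage margin; diagnosis, a primary outcome, was not.

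**Working it through.** **Inputs from the Sample size section:** margin .30, SD .83, one-sided alpha .05, power 80%, 95 per arm. **Input from the Abstract and Methods/design:** three primary outcomes and four post-baseline visits. **Assumption:** correlation between test statistics of 0.3 to 0.7, equal for all pairs. The article gives no correlation.

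**1. The plan's own figure.** With a true difference of zero,

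n per arm = 2 × (1.645 + 0.842)² × .83² / .30² = 94.6, rounded up to 95.

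The power at 95 per arm is Φ(.30 / (.83 × √(2/95)) − 1.645) = Φ(2.491 − 1.645) = 80.1%. The stated figure is reproduced exactly as a two-arm difference test on one continuous outcome. With SD 1.0 in place of .83 the formula gives 138, and with one-sided alpha .025 it gives 121, so neither of those was used.

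**2. Wording of the rule against the powered test.** The half-width of a one-sided 95% bound at 95 per arm is:

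- UP-TAU difference: 1.645 × .83 × √(2/95) = 0.198
- one arm alone: 1.645 × .83 / √95 = 0.140

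These are bounds on different quantities. Taken literally, the within-arm rule also behaves wrongly in either direction. If improvement is coded positive, UP passes only when its improvement is small. If improvement is coded negative, almost any improvement in UP passes, whatever TAU achieves.

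**3. Number of tests.** Three outcomes at four visits make 12 tests. The four tests on diagnosis have no applicable margin, which leaves 2 × 4 = 8.

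**4. If any one of the eight were enough.** With UP truly at the margin on every outcome and visit, the chance of at least one false pass at one-sided .05 is:

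| Assumed correlation | At least one of 8 passes |
|---|---|
| 0 (independent) | 1 − .95⁸ = 33.7% |
| 0.3 | 26.7% |
| 0.5 | 21.9% |
| 0.7 | 16.8% |

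**5. If BDI-II and BAI must both pass at one visit.** The type I error stays at or below 5%. Power at 95 per arm, with 80.1% for each test, is:

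| Assumed correlation | Both pass |
|---|---|
| 0 (independent) | .801² = 64.2% |
| 0.3 | 66.8% |
| 0.5 | 68.9% |
| 0.7 | 71.5% |

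**6. Scale of the margin.** The source effects (.4 to .8) are standardised, and half of their midpoint is .30. Used with an SD of .83, however, .30 corresponds to .30/.83 = .36 standard deviations. If .30 is meant as a standardised difference (SD 1), the power of one test at 95 per arm is 66.4%, and for both it is 48-55% at correlations 0.3-0.7. The figures in steps 1 to 5 take the article's SD of .83.

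**The case against.** The strongest reply is that the contrast is a slip of wording. The Sample size section defines the margin as a TAU-UP difference, the mixed model has group as a factor, between-group effect sizes are planned, and the Analyses section itself explains the design as UP being no worse than individual CBT. A literal within-arm rule could hardly be carried out. This stands as to intent: there is little doubt what is meant. It does not make the sentence correct, and the rule that decides the trial should not depend on inference from another section.

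A reader might infer that the plan allows a claim from any one of 12 tests. The document does not support that. It nowhere says that one success suffices. A separate conclusion per outcome, or a requirement that all pass, fits the text as well, and multiplicity may be handled in an analysis plan that is not shown. Nor can all 12 be counted, since the diagnosis has no margin. What remains is that the stated rule leaves the deciding test open.

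A reader might also infer that the sample size is wrong. It is not: 80% is right for the single comparison described. It fails to describe a claim that needs both symptom scales.

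Finally, one could argue that the pooled margin was meant for every outcome and can be converted to an odds ratio for diagnosis. The result depends on the scale of .30, which is unclear: by ln OR = d × π/√3, d = .30 gives 1.72 and d = .36 gives 1.93. Nor can the conversion be turned into a tolerated loss in recovery, because the article gives no recovery rate for TAU. The half to two thirds in its Background comes from studies of UP in group format. A conversion therefore does not replace a stated and justified margin.

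**Conclusion.** The point holds as a fault in a stated decision rule, and the correction needs no new data. The wording conflicts with the article's own definition of the margin and with the test that was powered. The intended UP-TAU contrast is recoverable, so this is an error of statement and not of design. The deciding outcome and visit are open, and each reading has a cost. An any-one reading, which is not excluded but also not stated, would carry a false-claim risk of about 17-27%. Requiring BDI-II and BAI together at one visit would bring power to about 67-71%. Both ranges rest on assumed equal correlations of 0.7 to 0.3 and on SD .83; the first also assumes UP exactly at the margin on both scales at all visits. The absence of an applicable margin for ADIS diagnosis follows from the text and needs no assumption. No joint power including diagnosis can be given until it has a margin.

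**What to change.** - State the rule on the contrast and give its direction: non-inferiority is concluded only if the one-sided 95% upper bound of the UP-TAU difference, with positive values meaning UP is worse, lies below the margin for both BDI-II and BAI at one named visit, for example post-treatment. Because both must pass, alpha need not be split.
- Label the other visits supportive. If durability is meant to decide, name a follow-up visit instead.
- State the scale of the .30 margin: raw with SD .83, or standardised.
- Keep the ADIS diagnosis as a reported outcome with its own justified risk-difference or odds-ratio margin, or label it supportive.
- Restate the power as joint power for BDI-II and BAI.

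The cost is a lower stated power and a documented amendment before unblinding. Relabelling a declared primary outcome is a substantive change and should be recorded with its date and reason. No new patients or data are needed.
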